### Trial data handling

Data are collected and maintained in accordance with the current legal and regulatory requirements. A data management protocol has been produced by the CTU to ensure secure data collection and storage in accordance with the Data Protection Act 1998, and later conforming to the General Data Protection Regulation 2016 and Data Protection Act 2018.

Electronic study records will be held over the lifetime of the study in secure storage solutions aligned with the host institution’s information security classification policy. At the time of writing, electronic study data are stored in an SQL server database on a restricted access, secure server maintained by the University of Plymouth. Data are entered into the database via a bespoke web-based data entry system encrypted using SSL V.3 (QuoVadis Global, http://www.quovadisglobal.com). Access to identifiable information is restricted and permission-based.

A parallel, linked, bespoke data system has been used to manage intervention engagement post-randomisation. The system captures all health trainer attempted and actual contact with intervention participants in real time to produce summary data (eg, number of sessions, duration and mode of sessions, notes on session content), and aid supervision sessions and intervention management (eg, should a health trainer be unavailable).

Identifiable information will be omitted from the transcriptions of the process evaluation interviews.

### Statistical analysis plan

A detailed statistical analysis plan was drafted during the trial delivery phase and will be approved by an independent statistician and wider Trial Steering Committee (TSC), prior to database lock. The analyses will be reported in full and in accordance with the Consolidated Standards of Reporting Trials (CONSORT) guidelines.^56^ The main planned analyses are summarised below.

### Baseline characteristics and summary statistics

Descriptive statistics by allocated group will be presented for the baseline, and primary and secondary outcomes, which includes the smoking outcomes and questionnaire data as well as the smoking and physical mediators, with the exception of the primary outcome and secondary abstinence measures (assessed at 3, 9 and 15 months only) and accelerometer outcomes (assessed only at 3 months).

For continuous outcomes, summary information will be presented in the form of means alongside SDs. Count and skewed continuous data will be presented in terms of median and IQR. For categorical outcomes, summary information will be presented in the form of frequencies and percentages.

Inferential statistical comparison at baseline of randomised groups is not good practice^57^ and it is expected that participants in both groups will, on average, be similar. Following initial primary analysis, if substantial imbalance at baseline is identified in any key variables, such as gender and age, the importance of any imbalance will be noted and additional adjusted analyses may be performed.

### Primary analysis

The null hypothesis is that there is no difference in CO verified 6-month prolonged floating abstinence rates between the intervention and control groups at 9 months post-baseline. In line with the Russell Standard schedule,^39^ the primary comparative analysis will be conducted on an ITT basis, in which participants with missing responses will be considered to still be smokers. Interpretation of the primary effectiveness analysis will be based on the OR from the logistic regression model adjusted for (fixed effect) stratification variables: site as a factor and HSI as an ordinal covariate. Both the adjusted (primary analysis) and unadjusted ORs and corresponding 95% CIs will be presented. Primary effectiveness shall also be presented as a relative risk along with the absolute between-group differences in abstinence rates, as recommended in the CONSORT guidelines for parallel group randomised trials.^58^

Planned sensitivity analysis of the primary outcome:

Rather than assuming participants with missing responses at 3 or 9 months were still smoking, the primary outcome will be imputed under a number of varying assumptions and the primary analysis re-run for each of the scenarios.A complier average causal effect analysis will be undertaken, if greater than 20% of participants allocated to the intervention group are categorised as not having completed at least two intervention sessions with a health trainer, with individual participants in the intervention group categorised as compliers if they completed at least two intervention sessions. Participants in the control group and non-compliers in the intervention group will be compared with compliers in the intervention group.

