### Determination of sample size

Since the planned primary analysis is a comparison of the proportions of the binary primary outcome, the sample size calculation was based on a two-sided Fisher exact test. An abstinence rate of 5% for the control group and detectable effect of 6% (ie, an increase from 5% to 11% due to the intervention) are conservative estimates consistent with those from the EARS pilot study^15^ and those reported from a systematic review of pharmacological interventions.^38^ The corresponding OR for this effect size is 2.35. Participants with missing outcome data will be assumed to be still smoking following the Russell Standard,^39^ and the numbers of participants in each allocated group are assumed to be in the ratio of 1:1. Under these conditions, according to Stata V.14.2, the minimum number of participants required to detect an abstinence rate of 11% compared with that of 5% in the control group, with a significance level of no more than 5% and power of at least 90%, is 900, above which a power in excess of 90% is maintained.

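### The sensitivity analysis labelled a complier average causal effect is worded as an as-treated comparison that randomisation does not protect

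*Protocol article*

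**What the plan says.** The analysis appears in the protocol article, section Primary analysis, in the list introduced as "Planned sensitivity analysis of the primary outcome". It is conditional: "A complier average causal effect analysis will be undertaken, if greater than 20% of participants allocated to the intervention group" have completed fewer than two health trainer sessions. Compliance is defined in one arm only, with "individual participants in the intervention group categorised as compliers if they completed at least two intervention sessions". The article then states which groups are set against each other: "Participants in the control group and non-compliers in the intervention group will be compared with compliers in the intervention group". It names no instrument, principal-stratification model or other estimator for this analysis.

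The main result does not depend on it, because "the primary comparative analysis will be conducted on an ITT basis, in which participants with missing responses will be considered to still be smokers".

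**The concern.** A CACE compares intervention compliers with the people in the control arm who would have complied if offered the intervention. Those people cannot be identified one by one, so the effect is recovered through random allocation. The stated contrast instead compares observed compliers with everyone else. The comparator mixes would-be compliers and would-be non-compliers, and moving the intervention non-compliers into it weights it further towards non-compliers.

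Attendance may well be prognostic here. The Intervention section lets participants decide how much support they take. Under Primary outcome measure, success needs carbon monoxide verification at face-to-face assessments at both 3 and 9 months, and missing responses count as smoking. People who skip sessions may also skip assessments and be scored as smokers whatever the intervention does.

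At stake is interpretation. A null ITT result beside a positive analysis labelled CACE would suggest that the intervention works for those who engage, under a label that readers take to rest on randomisation.

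**Working it through.** **The plan's own figure.** Under Determination of sample size, "the sample size calculation was based on a two-sided Fisher exact test", for "an increase from 5% to 11% due to the intervention", with 90% power, a 5% significance level and 900 participants. Exact enumeration of the two-sided Fisher test gives power 0.8995 with 449 per arm and 0.9003 with 450 per arm, so 900 reproduces. The odds ratio is (0.11/0.89)/(0.05/0.95) = 2.35, also as stated.

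**Inputs from the article.** 450 per arm, control abstinence 5%, design difference 6 points. The trigger implies a complier share c below 0.80.

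**Assumed, because the article gives neither figure.** c = 0.75 or 0.60, and r = 1, 2 or 3, where r is the untreated quit rate of would-be compliers divided by that of would-be non-compliers. Controls receive no health trainer sessions, and 0 or 1 session has no effect (the exclusion restriction).

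**Formulas.**
- Untreated rate in non-compliers: pn = 0.05/(c·r + 1 − c). In compliers: pc = r·pn.
- Comparator rate: [450 × 0.05 + 450(1 − c)·pn] / [450 + 450(1 − c)].
- CACE: ITT difference divided by c, which is 0.06/0.75 = 8.0 points at the design effect and 0 under no effect.
- Since 0.05 = c·pc + (1 − c)·pn, the contrast minus the CACE is pc − comparator = 2(1 − c)(pc − pn)/(2 − c). This is zero when pc = pn and takes the sign of pc − pn.

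**Results for c = 0.75.**

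| r | pn | pc | Comparator | Difference, no effect | OR, no effect | Contrast at design effect | CACE |
|---|---|---|---|---|---|---|---|
| 1 | 5.00% | 5.00% | 5.00% | 0 | 1.00 | 13.00 − 5.00 = 8.0 | 8.0 |
| 2 | 2.86% | 5.71% | 4.57% | +1.1 | 1.27 | 13.71 − 4.57 = 9.1 | 8.0 |
| 3 | 2.00% | 6.00% | 4.40% | +1.6 | 1.39 | 14.00 − 4.40 = 9.6 | 8.0 |

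Worked line for r = 2: pn = 0.05/1.75 = 0.0286. The comparator is (22.5 + 112.5 × 0.0286)/562.5 = 0.0457. The OR is (0.0571/0.9429)/(0.0457/0.9543) = 1.27.

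**Lower compliance.** With c = 0.60 and no effect, r = 2 gives 6.25% against 4.46% (OR 1.43), and r = 3 gives 6.82% against 4.22% (OR 1.66).

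**Scale against sampling error.** At c = 0.75, r = 2 and no effect, the standard error is √(0.0571 × 0.9429/337.5 + 0.0457 × 0.9543/562.5) = 1.5 points. The shift of 1.1 to 1.6 points is therefore about one standard error or less. At c = 0.70, a normal approximation puts the rejection rate of a nominal 5% test under no effect at about 14% (r = 2) and 22% (r = 3).

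**The case against.** The best defence is that the sentence loosely describes exposure coding. In an instrumental-variable CACE, treatment received is 1 for intervention compliers and 0 for controls and intervention non-compliers, which is exactly this split. The section Statistical analysis plan says that a detailed plan was drafted and that the article only summarises it, so the instrument may be specified there. This reading is possible and cannot be excluded without that plan. Even so, the article does more than leave the estimator open. It says which groups are to be compared, and an analyst who followed it would run the wrong comparison.

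Three further objections limit the point, and all stand:
- **Direction.** A reader might infer that the contrast must favour the intervention. Nothing in the article links attendance to prognosis. At r = 1 there is no bias, and at r below 1 its sign reverses. Taking few sessions in a participant-led programme need not mean low motivation.
- **The benchmark.** The 8.0 points rest on the exclusion restriction. If a single session helps, the ITT difference divided by c overstates the complier effect.
- **Reach.** A reader might infer that this analysis is certain to be reported, or is the only look at engagement. It runs only past the 20% trigger, and Secondary analyses also plans a model of the outcome on sessions attended within the intervention arm, although that too is non-randomised.

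**Conclusion.** The point holds as a fault in what the article fixes: the stated contrast is as-treated and does not match the CACE label. With 450 per arm, 5% control abstinence and 75% compliers, following it would give an odds ratio of 1.27 to 1.39 under no effect if would-be compliers are two to three times as likely to quit untreated. It would overstate the complier effect by 1.1 to 1.6 points at the design effect. With 60% compliers the null odds ratio is 1.43 to 1.66. These figures depend on the assumed compliance and r, and the discrepancy vanishes at r = 1.

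A reader might infer that the trial's main conclusion is compromised. The article does not support that: effectiveness is to be interpreted from the adjusted ITT logistic model, and neither that model nor the sample size uses this contrast. Severity is moderate.

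**What to change.** Replace the pooled-group sentence. State that the CACE will be estimated in all randomised participants, using allocation as the instrument for completing at least two sessions and adjusting for site and HSI. Two-stage least squares is one option; an equivalent structural mean or principal-stratification model would also serve. State the assumptions beside it: 0 or 1 session has no effect, and controls have no access to the health trainers. Check the estimate against the ITT risk difference divided by the complier share.

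If the pooled contrast is kept, call it as-treated and non-causal, and do not call it CACE.

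The cost is a change of wording and a few lines of code, with no new data. The article says that the statistical analysis plan was to be approved before database lock, so the wording belongs there. If that plan already specifies such an estimator, only the article's description needs correcting.

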### Secondary analyses

To explore whether the primary outcome was influenced by the intervention dose actually received (ie, number of health trainer sessions attended), the primary outcome shall be modelled on the number of health trainer sessions attended in the intervention group only, adjusting for the stratification variables. Although the trial is not powered to detect the influence of moderating factors on the primary outcome, secondary analyses will be undertaken to explore whether the intervention effect is modified by key demographic and/or behavioural factors at baseline. These are prespecified as the postcode-based Index of Multiple Deprivation (IMD); the factor indicating smoking cessation medication or a vaping product at baseline; MVPA level, confidence to quit; and the stratification variable, HSI. The multivariable logistic regression model outlined above will be extended to include the interaction term of allocated group and each of the listed potential modifying variables. Evidence of an interaction shall be interpreted through the 95% CIs of the coefficient for the interaction term.

During the development of this study, the potential health trainer effect was considered at length. Given the lack of evidence on individual health trainer effects, the study design and sample size calculations do not allow for such partial clustering within health trainers (within recruitment sites). However, an exploratory analysis of the intervention effect will be undertaken using a multilevel, mixed-modelling approach, to allow for the partially nested data: participants allocated to the intervention group will be partially clustered within the health trainer, in turn nested within sites.

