#### Baseline assessment

Participants then completed a baseline questionnaire with a member of the local study team either face-to-face, by mail or over the telephone. The schedule of measures and data collection at baseline and follow-up are shown in table 1.

**Table 1 T1:** Schedule of baseline and follow-up measures

	Screening and baseline	Month 3	Month 9	Month 15*
Demographics (eg, age, gender, education attained, employment status)	**X**			
Self-reported cigarettes per day (or equivalent)	**X**	**X**	**X**	**X**
Reduction of ≥50% in number of cigarettes smoked since baseline†		**X**	**X**	
Biochemically confirmed abstinence (self-reported quitters only)		**X**	**X**	**X**
Self-reported floating prolonged abstinence (since quitting smoking, with quit date, if relevant) over at least 6 months†			**X**	**X**
Accelerometer assessed minutes of moderate and vigorous physical activity in a subsample		**X**		
Self-reported 7-day recall of physical activity	**X**	**X**	**X**	
Heaviness of Smoking Index	**X**			
Use of smoking management products	**X**	**X**	**X**	**X**
Urge and strength of urge to smoke	**X**	**X**		
Engagement with the health trainer intervention (8 weeks, plus optional 6 weeks additional support if a quit attempt is made)		**X**		
Health and social care utilisation	**X**	**X**	**X**	
Health-related quality of life (EQ-5D-5L and SF-12)	**X**	**X**	**X**	
Self-reported weight and height (to calculate BMI)	**X**	**X**	**X**	
Self-reported process measures	**X**	**X**		
Importance and confidence in smoking reduction and cessation				
Importance and confidence in being physically active				
Action planning to change smoking				
Action planning to change physical activity				
Self-monitoring of smoking				
Self-monitoring of physical activity				
Availability of support to reduce smoking				
Availability of support to increase physical activity				
Use of physical activity for smoking regulation				
Serious adverse events (self-reported)		**X**	**X**	
Qualitative process evaluation (in parallel throughout) (sample)	**X**	**X**	**X**	**X**

*Only participants with biochemically verified abstinence at 9 months are followed-up at 15 months post-baseline.

†Derived measure.

BMI, body mass index; EQ-5D-5L, EuroQol-5 dimension-5 level; SF-12, 12-Item Short Form Health Survey.

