**Figure 2 F2:**
[figure not shown]
Indicative map of the TARS intervention components. TARS, Trial of physical Activity-assisted Reduction of Smoking.

Participants allocated to the intervention arm were offered individually tailored behavioural support from a health trainer. The health trainer delivered the processes outlined in figure 2 and table 2, with the option of up to eight weekly sessions, and a further six sessions if the participant wanted support after quitting, and aimed to empower participants to decide what support was offered, and where, when and for how long. Signposting to local smoking cessation support services was also offered to those wishing to quit. If a smoker wished to reduce smoking using e-cigarettes or licensed nicotine-containing products (LNCP), they were also offered any local available support for this.

Health trainers were appointed on the basis of having good communication skills, including empathy, and at least some training and experience in supporting health behaviour change. All health trainers had at least a first degree in a related field although this was not a prerequisite for the role. The health trainer was trained to support change in both smoking and PA and help individuals to make the connections between the two. As described in table 2, the core intervention processes that the health trainer was trained to deliver were: (1) building rapport and supporting autonomous behaviour change; (2) building motivation; (3) supporting self-monitoring and goal setting; (4) problem solving; (5) integrating smoking and PA behaviour; (6) supporting a health identity shift; (7) supporting the management of social influence on behaviours.

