#### Primary outcome measure

Biochemically verified 6-month floating prolonged abstinence between 3 and 9 months.^40^ Abstinence will be confirmed by expired CO <10 ppm measured with a CareFusion MicroCO metre (Williams Medical Supplies, Rhymney, UK, www.carefusion.co.uk) at a face-to-face visit.

Participants who self-reported abstinence at 3 months and who were confirmed as abstinent through biochemical verification via expired CO at a face-to-face assessment and then self-report abstinence (and not having smoked even a puff since the 3-month assessment) at 9 months, again confirmed by expired CO, will be defined as having prolonged abstinence over at least 6 months.

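### The exploratory dose analysis counts sessions that open only after a quit attempt, so dose is partly a consequence of the outcome and the per-session odds ratio does not measure the influence of dose

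*Protocol article*

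**What the plan says.** The Secondary analyses section of the protocol article sets out a dose analysis: "To explore whether the primary outcome was influenced by the intervention dose actually received", dose being the number of health trainer sessions attended. The model is fixed in the same sentence: "the primary outcome shall be modelled on the number of health trainer sessions attended in the intervention group only", "adjusting for the stratification variables". No time window is given, and sessions before and after quitting are not separated.

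The Intervention section describes the offer as "with the option of up to eight weekly sessions, and a further six sessions if the participant wanted support after quitting", a maximum of 8 + 6 = 14. Table 1 describes the second block as "plus optional 6 weeks additional support if a quit attempt is made".

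The primary outcome is "Biochemically verified 6-month floating prolonged abstinence between 3 and 9 months". It requires CO-confirmed abstinence at the 3-month assessment as well as at 9 months.

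**The concern.** Every success on the primary outcome has stopped smoking by 3 months and so qualifies for the second block of sessions. A participant who never tries to quit is limited to eight. A quitter can therefore accumulate sessions because of having quit, and the regression reads that as dose predicting abstinence. Site and the Heaviness of Smoking Index (HSI) are baseline variables and cannot remove an effect that runs from quitting to attendance.

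The stated question is causal: whether dose influenced the outcome. A per-session odds ratio that departs from 1 when sessions do nothing cannot answer it. A reader of the results could take it as evidence on how many sessions are worth offering.

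**Working it through.** **The plan's own figure.** The dose analysis has none. The sample size supplies the rates used here ("an increase from 5% to 11% due to the intervention") and it reproduces: OR = (0.11/0.89)/(0.05/0.95) = 2.348, and exact two-sided Fisher power is 0.8995 at N = 898 and 0.9003 at N = 900. The intervention arm is 900/2 = 450, with 450 × 0.11 = 49.5 expected successes.

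**Inputs from the article.** 450 participants; 11% abstinent; 22% attempting to quit (pilot, intervention arm); core sessions with mean 4.2 and range 0 to 8 (pilot).

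**Assumptions.** Uptake of the post-quit sessions is not given and is varied from 0 to 100% of those attempting to quit. Those who take them up attend a mean of 3 of the 6 (binomial). Core attendance is beta-binomial on 8 sessions, Beta(1.05, 0.95): mean 8 × 1.05/2 = 4.2, variance 6.65. Attendance is independent of quitting, so the true session effect is nil. Participants who attempt and relapse (22% − 11% = 11% of the arm) have the same access to extra sessions as successes.

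**Simulation of the planned model** (abstinence on total sessions, site and HSI; 1000 trials per row):

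| Uptake of post-quit sessions | OR per session | Significant and positive |
|---|---|---|
| 0% | 1.00 | 3% |
| 10% | 1.04 | 11% |
| 25% | 1.09 | 35% |
| 50% | 1.19 | 85% |
| 75% | 1.30 | 99% |
| 100% | 1.41 | 100% |

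The nominal rate in the positive direction is 2.5%.

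**Hand check at 50% uptake**, using log OR ≈ difference in mean sessions ÷ pooled within-group variance.
- Mean extra sessions among successes: 0.5 × 3 = 1.5.
- Mean extra among all others (relapsers included): 1.5 × 0.11/0.89 = 0.185.
- Difference: 1.5 − 0.185 = 1.315 sessions.
- Variance of extra sessions among those attempting to quit: 0.5 × (1.5 + 3²) − 1.5² = 3.00, so 9.65 in total for successes.
- Variance among all others: 6.65 + 0.1236 × 5.25 − 0.185² = 7.26.
- Pooled variance: 0.11 × 9.65 + 0.89 × 7.26 = 7.53.
- OR ≈ exp(1.315/7.53) = 1.19, as simulated.

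**Sensitivity.**
- 35% attempting to quit (more relapsers), 50% uptake: OR 1.15, 69% significant and positive.
- 5% abstinent, 50% uptake: OR 1.18, 52%.
- Quitters also stop core sessions at a random week: OR 0.83 at no uptake, 0.93 at 25%, 1.03 at 50%, 1.14 at 75% and 1.27 at 100%.

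**Candidate repairs under the same null.**
- Core sessions only: OR 1.00 if quitters keep attending the core phase, but about 0.83 if they stop at quitting.
- A bare count of pre-quit sessions: about 0.8, because quitting cuts the count short.
- Sessions in weeks 1 to 4 among those not yet quit (quit weeks assumed uniform over 1 to 12): OR about 1.0, with about 4% significant against a nominal 5%.

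**The case against.** The size and even the sign of the bias rest on two quantities the article does not report: uptake of the post-quit sessions, and whether quitters leave the core phase. The pilot range of 0 to 8 sessions is no evidence that anyone there went beyond eight. At 10% uptake the odds ratio is only 1.04, and with early departure from core sessions it can fall below 1. This objection stands. A reader might infer that a positive dose result is guaranteed, or that the model must show a strong effect even if sessions do nothing. The documents do not support that.

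A reader might also infer that only successful quitters can go beyond eight sessions. Table 1 makes a quit attempt the trigger, so relapsers qualify too. That dilutes the bias without removing it, and the table above already includes it.

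The analysis is labelled exploratory and sits within one arm, and nothing in the article says that it will guide commissioning. This stands as a limit on importance. The complier average causal effect analysis concerns receipt of at least two sessions and does not repair the dose model.

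Finally, the definition could be refined in the statistical analysis plan, which is not shown. But the article does not leave the exposure open: it defines dose as sessions attended, without restriction.

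**Conclusion.** The concern holds as a defect in an exploratory analysis. The exposure includes sessions unlocked by the event that defines the outcome, and the stated adjustment cannot correct for that, so the per-session odds ratio does not estimate the influence of dose.

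With no true effect, and with 450 participants, 11% abstinent and about 22% attempting to quit, the odds ratio runs from about 1.0 (no uptake) through 1.1 to 1.2 (25 to 50% uptake, mean 3 extra sessions) to about 1.4 (full uptake). In the middle range roughly 35 to 90% of trials would be falsely significant, the exact share depending on the attendance distribution assumed. If quitters also stop core sessions early, most scenarios give about 0.8 to 1.1. Uptake and early departure are assumptions throughout.

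The randomised primary comparison and the sample size are not affected. The change is worth making before database lock but does not threaten the trial's main conclusion.

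**What to change.** Define dose as the number of sessions attended within a fixed early landmark period, for example the first 4 weeks after randomisation, and model the primary outcome among intervention participants who had not quit by the landmark. Apply the exclusion to every quit attempt dated before the landmark, whether or not it lasted. Do not substitute a bare count of pre-quit or core sessions, because quitting truncates both. Report the result as an association that may still be confounded by motivation, and drop the wording about influence.

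The cost is a change of wording in the analysis plan. The contact system described under Trial data handling logs health trainer contacts in real time, and Table 1 lists the quit date among the self-reported items. The price is precision and scope: early quitters leave the analysis, so it has fewer than the roughly 50 expected events. If quit weeks were uniform over 1 to 12, for instance, about 49.5 × 8/12 = 33 would remain. The result would then describe later quitting only.
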